**Methods:**

Our cohort consisted of women over 40 years of age with primary knee osteoarthritis, according to the American College of Rheumatology clinical criteria. Primary outcome was blinded measurement of cartilage morphology via magnetic resonance imaging scan of the tibiofemoral joint. Secondary outcomes included walking endurance, balance, muscle strength, endurance, power, and velocity, body composition, pain, disability, depressive symptoms, and quality of life.

Participants were randomized into a supervised progressive resistance training or sham-exercise group. The progressive resistance training group trained muscles around the hip and knee at 80% of their peak strength and progressed 3% per session, 3 days per week for 6 months. The sham-exercise group completed all exercises except hip adduction, but without added resistance or progression. Outcomes were repeated at 3 and 6 months, except for the magnetic resonance imaging scan, which was only repeated at 6 months.

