### Definitions

Session compliance was defined as the number of sessions attended out of 78 available sessions (up to 1 month extension was given to make up any missed sessions during the 6-month intervention). Training intensity compliance was defined as the difference between the theoretical relative load and the actual relative load for exercise for each session. The theoretical relative load (relative to the most recent 1RM) and the actual relative load was calculated at 4, 8, 12, 16, 20, 24, and 26 weeks. The actual load was then subtracted from the theoretical relative load to get difference in relative loads. Difference should be equal to zero if training intensity compliance was perfect or the results will be negative if actual was greater than theoretical. A one sample t-test was then performed to see whether or not the difference in loads was significantly different than "zero", the ideal value.

Total tonnage per exercise was calculated by summating the training load by the number of repetitions completed for that exercise for the intervention (24 repetitions for 78 sessions (total of 1872 repetitions) per exercise for the PRT group and 16 repetitions for 78 sessions (total of 1248 repetitions) per exercise for the sham-exercise group).

Whole body total tonnage was calculated by summating the total summated loads of each exercises and multiplying that by the total number of repetitions of all exercises.

Dropouts were those participants who did not complete the intervention and did not complete their final assessment (i.e. loss to follow-up). Discontinued subjects were those who did not complete the intervention, but did complete their final assessment and were included in the complete case analysis.

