### Statistical analysis

Data were inspected for normality visually and statistically (skewness -1 ≥ 1), and expressed as mean and standard deviation or median and range, as appropriate. Non-normally distributed data were log-transformed prior to use with parametric statistics if possible or used with non-parametric tests if assumptions of normality were not met despite transformation. Our primary analytic strategy was a complete case analysis because of the novelty of our primary outcome. Our secondary sensitivity analysis was intention-to-treat with data imputed via the expectation maximization algorithm (covariates included in the model were group, baseline score, and compliance). Comparisons between groups were made using repeated measures analysis of co-variance (ANCOVA) for both time and group × time interactions, and ANCOVA models for % change scores adjusted for baseline value of each outcome for normally distributed continuous data. Additional covariates considered for inclusion in these models were characteristics at baseline which were different between groups and related to the dependent variable of interest. The Kruskal-Wallace test or Mann-Whitney U test were used for non-normally distributed continuous data. SPSS (Release 13.0 for Windows, 2004, Chicago: SPSS Inc) was used for all data analysis. All *P *values of less than 0.05 were considered statistically significant except for post-hoc comparisons of pairs of variables from significant Kruskal-Wallace models, which were adjusted for multiple comparisons using the method of Bonferroni. Clinical meaningfulness of differences observed was assessed by evaluation of the magnitude of the differences relative to clinical outcomes in the literature, and calculations of effect sizes (Formula 1) adjusted via Hedges bias-corrected effect size for small sample sizes [56]. Effect sizes were interpreted according to Cohen's interpretation of 'trivial' ( < 0.20), 'small' (≥ 0.20 < 0.50), 'moderate' (≥ 0.50 < 0.80), and 'large' (≥ 0.80) effect size [56]. Caution was taken when using Cohen's interpretations as these were originally based on psychological studies. 95% confidence intervals (CIs) for the relative ES were calculated.

$$\begin{array}{cc} \text{Effect Size}=\frac{\Delta \text{ Treatment}-\Delta \text{ Control}}{\text{Pooled SD}} & \left(\text{Formula }1;(56)\right) \end{array}$$

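### For three-visit secondary outcomes, the complete-case repeated measures ANCOVA can drop finishers who missed 3 months and leaves later leavers' 3-month data unused

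*Protocol article*

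**What the plan says.** The Methods paragraph of the abstract gives the schedule: "Outcomes were repeated at 3 and 6 months, except for the magnetic resonance imaging scan, which was only repeated at 6 months". Walking, strength, symptom and questionnaire outcomes therefore have three visits, and the MRI outcome has two.

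The Statistical analysis section sets the primary analysis set and its reason: "Our primary analytic strategy was a complete case analysis because of the novelty of our primary outcome". For normally distributed outcomes it names two models. One is a repeated measures model: "Comparisons between groups were made using repeated measures analysis of co-variance (ANCOVA) for both time and group × time interactions". The other works on the change from baseline: "ANCOVA models for % change scores adjusted for baseline value of each outcome for normally distributed continuous data". Other continuous data go to rank tests: "The Kruskal-Wallace test or Mann-Whitney U test were used for non-normally distributed continuous data". The sensitivity analysis is described as follows: "Our secondary sensitivity analysis was intention-to-treat with data imputed via the expectation maximization algorithm (covariates included in the model were group, baseline score, and compliance".

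The Definitions section says of discontinued women that they did not finish the intervention "but did complete their final assessment and were included in the complete case analysis". It classes as dropouts those who completed neither the intervention nor the final assessment.

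The article names no mixed or likelihood model that would use partial records.

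**The concern.** Classical repeated measures ANCOVA over three visits works on complete rows. Whether baseline is a level of the time factor or a covariate, a woman without a 3-month value leaves the group × time test. Three things follow.

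- **Different women in different tests.** A discontinued woman who missed 3 months and returned at 6 belongs to the complete case analysis under Definitions, but not to the group × time test. The % change ANCOVA at 6 months would keep her, so the two named models can run on different women.
- **A reason that does not reach these outcomes.** Novelty of the MRI measure gives no ground for setting aside recorded values of the 6-minute walk, 1RM, WOMAC or SF-36.
- **Unused information on leavers.** A woman who attends at 3 months and then leaves contributes nothing to the primary analysis. If leaving depends on how she was doing at 3 months, that value is what could correct the 6-month comparison.

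At stake are the secondary efficacy hypotheses on physical performance and symptoms. They would be tested on the women easiest to follow.

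**Working it through.** **Inputs from the article.** Target sample 63 and anticipated dropout 20% (Sample Size); three visits for non-MRI outcomes (abstract, Methods). The article gives no figure for the effect of missed visits, so there is none to reproduce. Visit correlations, secondary effect sizes and the share of missed 3-month visits are not given and are assumed below.

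**Step 1. Finishers dropped.** With 20% of 63 lost, 63 × 0.80 = 50.4 women have a final assessment. If a share m of them lacks the 3-month visit, listwise deletion keeps 50.4 × (1 − m):

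| m (assumed) | Kept | Dropped |
|---|---|---|
| 5% | 47.9 | 2.5 |
| 10% | 45.4 | 5.0 |
| 15% | 42.8 | 7.6 |

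The standard error ratio is about √(1/(1 − m)). At m = 10% it is √(1/0.90) = 1.054, about 5% wider.

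**Step 2. Leavers' 3-month values unused.** Leavers number 63 × 0.20 = 12.6. If 25%, 50% or 75% of them (assumed) had a 3-month visit, 3.2, 6.3 or 9.5 women's 3-month records go unused.

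**Step 3. Bias when some leavers also lack a 3-month value.** Simulation of 2,000 trials of 63 women. Assumptions: all visit correlations 0.6; true effect 0.35 SD at 3 months and 0.60 SD at 6 months; 3-month value missing in 10% of finishers and 50% of leavers. Mean 6-month estimate:

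| Leaving | Listwise, three visits | 6-month ANCOVA | Likelihood, all visits |
|---|---|---|---|
| Random | 0.608 | 0.609 | 0.609 |
| PRT arm: likelier with poor 3-month score | 0.657 | 0.659 | 0.629 |

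With random leaving, the SD of the estimate is 0.241, 0.230 and 0.229 respectively; 0.241/0.229 = 1.05, which agrees with step 1. Monte Carlo error of each mean is about 0.23/√2000 = 0.005, so the random row shows little or no bias. In the selective row the excess is 0.657/0.60 − 1 = 9.5% listwise, 9.8% for the 6-month ANCOVA, and 0.629/0.60 − 1 = 4.8% for the likelihood model.

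**Step 4. Bias when every leaver has a 3-month value.** Simulation of 400,000 women. Assumptions: correlations 0.6 (baseline to 3 months), 0.6 (baseline to 6) and 0.7 (3 to 6); true 6-month effect 0.40 SD; 20% loss after 3 months in each arm; loss in the PRT arm rising with poor 3-month response (logit slope per SD of residual response).

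| Slope | Complete-case ANCOVA | Using the 3-month value |
|---|---|---|
| 0 (unrelated) | 0.398 | 0.399 |
| 1 | 0.469 | 0.398 |
| 2 | 0.513 | 0.403 |

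The excess is 0.469/0.40 − 1 = 17% and 0.513/0.40 − 1 = 28%. A separate run with 3-month effects of 0.2, 0.3 and 0.4 SD gave 0.47 and 0.50 to 0.51 for complete cases.

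**Step 5. Does the sensitivity analysis repair this?** Under the step 4 assumptions, imputing 6-month values from group and baseline alone gave the same 0.47 and 0.50 to 0.51 as complete cases. Compliance, the third listed input, was not modelled. It would help only as far as it stands in for 3-month response.

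**The case against.** The best case for the plan has four parts.

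- **Other analyses are named.** A reader might infer that every non-MRI outcome is tested only by the repeated measures model. The article does not support that. The % change ANCOVA keeps finishers with baseline and 6-month data, and outcomes that stay non-normal go to rank tests. The point is limited to normally distributed three-visit outcomes.
- **The misfit with Definitions is conditional.** A reader might take it as a flat contradiction. It is not. Listwise deletion is inferred from complete cases plus repeated measures ANCOVA and is nowhere stated. The inclusion sentence concerns discontinued women, so the misfit arises only for one who missed 3 months and returned at 6. A condensed article may also leave the handling of a missed interim visit to a fuller document. That silence is not the complaint; the named method and its stated reason are.
- **An imputed intention-to-treat analysis exists.** It does retain both groups of women. But it is secondary, and its listed inputs leave out the 3-month score, so it need not correct loss that depends on 3-month response.
- **The size is assumed.** This stands. A reader might treat 17% to 28% as the expected bias. Only the 20% dropout comes from the article, and that range needs every leaver to have a 3-month value and selective loss in one arm. Step 3 also shows that the bias comes from ignoring leavers' 3-month data, not from dropping finishers: listwise and 6-month ANCOVA agree (0.657 and 0.659). Nor is a likelihood model always unbiased, since it still gave 0.629 against 0.60.

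**Conclusion.** The concern holds in limited form, for normally distributed secondary outcomes measured at baseline, 3 and 6 months. Their primary analysis rests on complete cases for a reason that applies only to MRI. In its classical form it drops finishers without a 3-month visit and leaves later leavers' 3-month data unused, and the planned sensitivity analysis need not make this good.

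With random loss the cost is precision, about 5% if 10% of finishers miss 3 months. With one-arm loss that depends on 3-month response, the illustrations give a bias of about 10% to 28% in the 6-month effect. A likelihood model halves it at the lower end (half of leavers without a 3-month value) and removes it at the upper end (all leavers with one). These figures show what could happen; they are not estimates for this trial. The MRI outcome, with two visits, is untouched by this argument. Whether complete cases suit the MRI outcome is a separate question.

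**What to change.** For outcomes measured at both 3 and 6 months and analysed as normal, replace the repeated measures ANCOVA by a linear mixed model:

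- responses: the 3- and 6-month values;
- fixed effects: baseline value, group, visit and group × visit;
- unstructured within-woman covariance;
- every randomised woman with at least one follow-up value included;
- treatment effect read as the group contrast at 6 months.

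Limit the complete-case rationale to the MRI outcome. If the imputed sensitivity analysis is kept for these outcomes, its inputs should include the 3-month score.

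The cost is a change of wording and a different procedure on data already collected. The downside is reliance on missing at random: women who leave without a 3-month value are still not corrected for if their leaving depends on response.

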### Covariates

Covariates identified *a priori *included age, BMI, duration of OA, use of glucosamine and/or chondroitin sulfate, number of chronic diseases. Other covariates will be selected if potential confounders are identified amongst baseline participant characteristics.

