### Randomization

Using a computerized randomization program , a co-investigator uninvolved in participants testing or training randomly allocated participants into 1 of 2 groups. Participants were stratified according to glucosamine and/or chondroitin use (current or within the past 6 months) and Physical Function (Section C; Disability) WOMAC score (< or > 27) in order to equalize these potential confounders between groups. After completion of baseline assessments, participants were given a sealed envelope containing the allocated group (A or B) in accordance with the randomization sequence.

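### The covariate rule makes the adjusted model depend on observed baseline imbalance, is not reconciled with the a priori list, and tends to keep the randomisation strata out

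*Protocol article*

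**What the plan says.** Three sections of the protocol article bear on the adjusted model.

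- **Statistical analysis.** The between-group comparison of change uses "ANCOVA models for % change scores adjusted for baseline value of each outcome". Further covariates considered for these models are "characteristics at baseline which were different between groups and related to the dependent variable of interest". The text gives no threshold for either condition and no candidate list, and it mentions neither the a priori list nor the randomisation strata.
- **Covariates.** The a priori covariates are "age, BMI, duration of OA, use of glucosamine and/or chondroitin sulfate, number of chronic diseases". The section then adds: "Other covariates will be selected if potential confounders are identified amongst baseline participant characteristics".
- **Randomization.** "Participants were stratified according to glucosamine and/or chondroitin use (current or within the past 6 months") is the first factor. The second is the physical function section of the "WOMAC score (< or > 27) in order to equalize these potential confounders between groups".

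**The concern.** In a randomised trial, baseline differences between arms arise by chance. A covariate earns its place because it is prognostic or was used in the randomisation, not because it happened to differ. The second condition of the rule, association with the dependent variable, can be judged only once outcome data are available, and separately for each outcome. The set of adjusters is then itself a result of the trial, and the reported interval takes no account of how it was chosen.

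The rule also works against the design. The trial stratified on two factors because it regarded them as potential confounders. Stratification makes them similar between arms, so a test for difference between groups will seldom let them in. An analysis that ignores prognostic strata estimates its standard error from residual variance that the design has already removed from the comparison. The interval is then too wide and power is lost, in a trial with a target of 63 women.

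Finally, the two sections on covariates cannot be combined into one model. A reader cannot tell whether age, BMI, disease duration, supplement use and number of chronic diseases are in the primary analysis always, sometimes or never.

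**Working it through.** The plan gives no figure for the covariate rule, so there is none to reproduce. The check takes the texts first and then the size of the effect.

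**1. Where each variable stands**

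| Variable | Randomisation stratum | A priori list | Fixed in the ANCOVA |
|---|---|---|---|
| Baseline value of the outcome | no | no | yes |
| Glucosamine/chondroitin use | yes | yes | not stated |
| WOMAC function | yes | no | only when it is itself the outcome |
| Age, BMI, OA duration, chronic diseases | no | yes | not stated |

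**2. How often the rule would act**

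The chance that at least one of five independent covariates differs at p < 0.05 is 1 − 0.95⁵ = 0.226. The rule was simulated with 5,000 trials per scenario and 50 completers (63 × 0.8 = 50.4). Both conditions were set at p < 0.05, which is an assumption because the plan gives no threshold. With five candidates the rule changed the model in 1% to 16% of trials. With eight candidates and looser cut-offs (0.20 and 0.10) it did so in 70%. How far the model depends on the data is thus set by thresholds that the text does not state.

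**3. Omitting prognostic strata, general case**

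If balanced strata explain a share R² of the within-arm variance, the standard error from a model without them is too large by the factor 1/√(1 − R²). The true type I error is then P(|t| > t₀.₉₇₅ × factor), here with 48 degrees of freedom. The R² values are assumed.

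| R² | SE factor | True type I error at nominal 0.05 |
|---|---|---|
| 0.10 | 1.05 | 0.039 |
| 0.20 | 1.12 | 0.029 |
| 0.30 | 1.20 | 0.020 |

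**4. Glucosamine alone, from the sample-size reasoning**

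Inputs from the Sample Size section: change of −2.8% under sham and −0.56% under training, SD 2.7 (variance 7.29), and full protection by glucosamine. Assumptions: a share f of women are users and lose nothing, non-users follow the stated means, and 2.7 is the SD within a stratum.

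- Difference between users and non-users: 2.8 under sham, 0.56 under training, average 1.68.
- f = 0.2, so f(1 − f) = 0.16. Variance under sham is 7.29 + 0.16 × 2.8² = 8.54; under training 7.29 + 0.16 × 0.56² = 7.34; mean 7.94. R² = 0.16 × 1.68² / 7.94 = 0.057, and the SE factor is 1/√0.943 = 1.03.
- f = 0.4, so f(1 − f) = 0.24. The variances are 9.17 and 7.37; mean 8.27. R² = 0.24 × 1.68² / 8.27 = 0.082, and the SE factor is 1/√0.918 = 1.04.

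**5. Power**

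Same simulation, true difference 2.24 (2.8 − 0.56), SD 2.7. Stratum prevalences of 40% and 50% and all correlations are assumed.

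| Correlation with outcome | Type I error, stated rule / strata included | Power, stated rule / strata included |
|---|---|---|
| strata 0, covariates 0 | 0.050 / 0.051 | 0.82 / 0.82 |
| each stratum 0.3, covariates 0 | 0.035 / 0.055 | 0.83 / 0.88 |
| each stratum 0.4, five covariates 0.25 each | 0.016 / 0.048 | 0.84 / 0.93 |

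In the middle row the average model SE under the rule is 0.77, while the estimate actually varies with SD 0.72. With the strata included, the model SE is 0.70.

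**The case against.** The strongest reply is that this is a condensed article, so its silence about a model term proves nothing, and that any error is modest and conservative. Part of this stands. Had the article simply not mentioned the strata, there would be no finding. But it states a selection rule, and that rule is open to criticism as written.

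Several stronger readings are tempting, and the document does not support them.

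- *The analysis section contradicts the a priori list.* It does not. The Covariates section itself allows later additions, and the extra covariates in the analysis section may be meant as additional to that list. The two sections are unreconciled.
- *Both strata are excluded.* No sentence excludes them, and glucosamine/chondroitin use is on the a priori list. Only WOMAC function is on no list.
- *Glucosamine use is the strongest known predictor of cartilage loss.* The Sample Size section uses a glucosamine trial to benchmark the training effect and ranks no predictors. Looking at the sham arm alone would give an R² of 0.15 to 0.21, but the standard error of the comparison depends on both arms, where the figure is 0.057 to 0.082. The premise also fits the plan imperfectly: with users at zero loss, the sham mean would be −2.24% (f = 0.2) or −1.68% (f = 0.4), not −2.8%.
- *The rule inflates false positives.* In the simulations it did not: type I error was 0.008 to 0.035 where strata were prognostic and about 0.05 where nothing was. A search for the smallest p-value over all 32 subsets of five covariates would give 0.10 to 0.18, but the plan describes no such search and its imbalance condition narrows the choice.
- *A score of exactly 27 had no stratum.* This looks like a slip of notation, and nothing suggests that anyone went unallocated.

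**Conclusion.** The point holds as a should-fix. The text does not determine the adjusted model: one term is fixed, and the rest depend on observed imbalance and on association with each outcome, without thresholds. The standing of the five a priori covariates is unclear. The rule tends to keep out the factors used to stratify.

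The demonstrated harm from leaving out the strata is lost precision. The standard error is about 3-4% too large on the glucosamine premise with 20-40% users, and about 5-20% too large if the strata explain 10-30% of variance. In the middle simulated scenario, power is 0.83 instead of 0.88. User prevalence, R² and correlations are assumptions, since the article gives none of them. If the strata carry no prognostic information, precision is hardly affected, and what remains is that the model is chosen from the data.

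**What to change.** 1. In Statistical analysis, prespecify one primary ANCOVA with arm, the baseline value of the outcome, and both randomisation strata (glucosamine/chondroitin use and WOMAC function) as applied at randomisation.
2. Put the remaining a priori covariates (age, BMI, duration of OA, number of chronic diseases) in one prespecified sensitivity model.
3. Delete selection by baseline difference from both the Covariates and the Statistical analysis sections, so that the two describe the same models.

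The cost is two degrees of freedom, about 47 to 45 residual with 50 completers, and some wording. No new data are needed: both factors were recorded before allocation, and the article places the primary results in the future.
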